## Abstract

**Background:**

Depression can be treated in an outpatient, inpatient or day hospital setting. In the German health care system, episodes of inpatient or day hospital treatment are common, but there is a lack of studies evaluating effectiveness in routine care and subgroups of patients with a good or insufficient treatment response. Our study aims at identifying prognostic and prescriptive outcome predictors as well as comparative effectiveness in psychosomatic inpatient and day hospital treatment in depression.

**Methods/Design:**

In a naturalistic study, 300 consecutive inpatient and 300 day hospital treatment episodes in seven psychosomatic hospitals in Germany will be included. Patients are assessed at four time points of measurement (admission, discharge, 3-months follow-up, 12-months follow-up) including a broad range of variables (self-report and expert ratings). First, the whole sample will be analysed to identify prognostic and prescriptive predictors of outcome (primary outcome criterion: Quick Inventory of Depressive Symptoms QIDS-total score, expert rating). Secondly, for a comparison of inpatient and day hospital treatment, samples will be matched according to known predictors of outcome.

**Discussion:**

Naturalistic studies with good external validity are needed to assess treatment outcome in depression in routine care and to identify subgroups of patients with different therapeutic needs.

**Trial registration:**

Current Controlled Trials ISRCTN20317064

## Background

Depression is one of the most common diseases with a life time prevalence rate of 17.1% and a 12-months prevalence of 10.7% [1]. It is a leading cause of disability worldwide [2]. The German health care system provides outpatient, inpatient and day hospital care for depression [3]. Two medical specialties are involved in the treatment of mental disorders: psychiatry and psychosomatic medicine. Psychosomatic inpatient and day hospital treatment programs are characterized by a stronger focus on psychotherapy as the main treatment modality, integrating psychopharmacological and somatic treatment elements. About 40-50% of the patients treated in psychosomatic hospitals have a main diagnosis of major depression [4-6]. In contrast to many other countries, inpatient treatment plays an important role: ~64.500 beds are provided in psychiatric and ~6400 in psychosomatic hospitals for acute care, with an additional 15.400 beds in psychosomatic rehabilitation hospitals, covering a considerable part of health care for people with mental diseases.

In comparison to outpatient treatment, hospital programs have the advantage of using a multimodal approach, combining daily structure with individual, group and additional treatment components [5]. Day hospital programs for acute psychosomatic care are comparable to inpatient programs with the difference that patients return home at evenings and weekends. There is an increasing interest in day hospital programs, because of the lower costs of this treatment modality [7,8].

Although treatment of depression is a high priority task in psychosomatic medicine as well as in psychiatry, there is a lack of studies on inpatient or day hospital treatment. Additionally, previous studies do not take into account the marked heterogeneity of patients with this diagnosis: Depression in one subject is not like depression in another (“uniformity myth”; [9]). This will be especially true for the patient group treated in inpatient and day clinic units, who show high rates of co-morbidity with mental or somatic disorders, a severe course of the illness or complex problems including the social and family situation. It can be postulated that tailoring treatments to the needs of subgroups of patients with special characteristics will improve overall outcome, which is reported to lie around a mean value of 30-40% remission rates after “standard treatment” for depression [3].

There are few naturalistic studies describing effects of psychosomatic inpatient and day hospital treatment, mostly lacking follow-up assessments and a detailed description of patients characteristics (personality, co-morbidity) [4-6,10-12]. The majority of studies report on heterogeneous samples including depressed patients besides other diagnoses. There is no study trying to identify subgroups of patients with a main diagnosis of major depression with different symptom courses and no study comparing inpatient and day hospital treatment. The same is true for psychiatry, with a limited number of studies on this topic conducted in the German health care system (see for example: [13-15]).

The following predictors were repeatedly found to be associated with the course and overall outcome in depression: (1) number of episodes of major depression (MDE), (2) duration of the current MDE, (3) co-morbidity (mental, somatic) and (4) incomplete remission of the last episode of MDE or “double depression” [3]. A higher probability for a relapse is associated with younger age, female gender, a lack of social support and being single. An additional somatic illness and a late onset of treatment are able to nearly completely explain prognosis in a higher age group [16]. Traumatic childhood experiences were also identified as a risk factor for depression and important to consider in terms of the long term course and risk for relapse [17]. Most of these factors have been found in studies on outpatient treatment for depression. It remains unclear, if the same predictors will be identified analysing samples of patients treated within an inpatient or day hospital setting.

Another group of studies focusses on the influence of personality characteristics on the course and prognosis of depression. One of the most relevant concepts in this field is the one of Sydney Blatt, who postulated a two-dimensional model, which differentiates between depressed patients who primarily deal with problems in interpersonal relatedness (“anaclitic”: fears of abandonment; dependency) and those preoccupied with self-definitional issues (“introjective”: hash self-criticism; perfectionism) [18]. There is an ongoing debate on the relevance of this theoretic model^a^. In support of it, perfectionism as a trait was repeatedly found to be associated with a more problematic course in depression. Overall, it can be assumed that personality traits and other patient variables (social support, interpersonal problems, etc.) are not only overall predictors of outcome, but also interact with the form of treatment or setting provided.

Studies comparing inpatient and day hospital treatment found comparable outcomes for patients with mental disorders, for whom both settings are suitable [8]. We could replicate this finding for a psychosomatic clinic in Germany [11], but found differences in effects when analysing outcome for single diagnostic categories like eating disorders [19,20]. Comparing means of large samples might cover differences between subgroups, which can be better treated in one or the other setting. In a pilot study, we tried to identify predictors of differential outcome of inpatient and day hospital treatment and found a higher motivation for psychotherapy and higher burdens at home to be associated with a good outcome after day hospital treatment, whereas strong wishes to give up responsibility for oneself were associated with an unfavourable course of inpatient treatment [5,21]. Strong wishes to give up responsibility might be associated with “anaclitic” features according to S. Blatt et al. [18], but this has to be shown empirically.

The INDDEP (**In**patient and **D**ay Hospital Treatment for **Dep**ression) - study is a naturalistic study which aims at the description and comparison of symptom courses after psychosomatic inpatient and day hospital treatment for major depression. It further aims at identifying “prognostic” (associated with general outcome) and “prescriptive” (associated with the differential outcome in both settings) variables, which can help to discriminate subgroups of patients with differences in course and treatment needs [22]. Finally, we aim to go beyond previous studies in assessing not only socio-demographic variables and aspects of depressive symptomatology, but also personality traits, coping style and interpersonal problems as possibly relevant predictors.

## Methods

For to analyse a sample which represents the clinical reality of psychosomatic inpatient and day hospital treatment for depression in Germany (external validity), we did not choose a randomized design as we expected only a minority of patients to agree to a randomization procedure and expected considerable resistance in non-university centres. Therefore, the study is naturalistic in nature and composes two steps: I) an analysis of predictors in the whole sample and II) a comparison of inpatient and day clinic treatment in a quasi-experimental design. For a comparison of inpatient and day clinic treatment, samples will be parallelized according to known predictors of outcome (see: methods against bias).

### Study centers

The study is carried out at 7 German study sites. These comprise three psychosomatic departments at university hospitals and four clinics outside the university context. All departments or clinics provide a treatment program that is typical for clinics of psychosomatic medicine in Germany (see [5,21]). Participating centers are the Department of Psychosomatic Medicine and Psychotherapy at the University Clinic of Freiburg, the Clinic of Psychosomatic Medicine and Psychotherapy at the University of Ulm, the Department of Psychosomatic Medicine and Psychotherapy at the University Clinic of Mainz, the Clinic for Psychosomatic Medicine and Psychotherapy at the Robert-Bosch-Krankenhaus Stuttgart, the Thure-von Uexküll-Klinik Freiburg, the Clinic for Psychosomatic Medicine and Psychotherapy at the Bürgerhospital in Stuttgart and the Rhein-Klinik, Bad Honnef.

### Participants

During a 2.5-year recruitment period, all patients admitted to the participating clinics will be screened for depressive symptoms and inclusion and exclusion criteria checked. Recruitment will be continued until a sample of 300 patients is reached in each setting (inpatient, day hospital). There has to be a minimum of 35 patients per setting in each centre to control for centre effects. Research assistants will be involved, if a depression can be identified as the main reason for admission or the most dominant problem (main diagnosis). The research assistant will inform the patient about the study and check inclusion and exclusion criteria. Inclusion and exclusion criteria are listed in Table 1. Patients will get comprehensive information about the study and are included after written consent. There is permission from the local ethics committees.

**Table 1 T1:** Inclusion and exclusion criteria of the INDDEP-study

Inclusion criteria	• MDE (major depressive episode, unipolar, according to DSM IV) as main diagnosis
	• age 18-65
	• QIDS-C score > 10
	• informed consent
	• sufficient knowledge of German language
Exclusion criteria	• psychotic disorder (current or life time)
	• bipolar disorder
	• substance dependency (current or last three years)
	• current suicidal ideation
	• antisocial personality disorder
	• cognitive impairment, dementia
	• admission for diagnostic reasons (not for treatment)
	• second admission during recruitment period

### Interventions

Interventions comprise the routinely provided inpatient and day hospital treatment programs of psychosomatic clinics in Germany. These include individual and group psychotherapy, art and body therapy, relaxation therapy, family sessions and support of a social worker if needed, psychopharmacology, educational elements, physician rounds and medical care (see [5]). Treatment duration usually comprises between 4 and 12 weeks [5].

### Measurement time points

Time points of measurement will be the time point at admission (T0), at discharge (T1), a three months follow-up (T2) and a 12 months follow-up (T3). Data will include a detailed assessment on different levels: symptomatology (characteristics of depression and co-morbid conditions), general disturbance and quality of life, aspects of personality, interpersonal problems and a further aspects that has been identified to influence the course of depression: traumatic childhood experiences. Variables will be grouped into classes of possible predictors. A combination of self-report and assessments by independent, trained research assistants will be used (see Table 2).

**Table 2 T2:** Instruments used the INDDEP study

**Time point of measurement**	**Outcome/Variables**	**Patient**	**Research assistant**
		**(self-report)**	**(expert rating)**
**T0 **(admission)	Depressive symptomatology:	QIDS-SR	QIDS-C, SKID-I
	Co-morbidity		SCID I + II
	Personality, interpersonal problems, mode of coping:	IIP-32, DEQ, DAS	
	Overall disturbance and functioning:	SCL-90-R	SOFAS
	Social support:	F-SozU K-14	
	Quality of Life:	SF-12	
	Traumatisation:	CTQ	
**T1 **(discharge)		QIDS-SR	QIDS-C
		SCL-90-R	SOFAS
		IIP-32	
**T2 **(3-months Follow-up) and **T3 **(12-months Follow-up)		QIDS-SR	QIDS-C, LIFE-Interview
		SCL-90-R	SOFAS
		SF-12	
		IIP-32	

QIDS-SR = Quick Inventory of Depressive Symptoms, self-report form [23], QIDS-C = expert rating; SCID-I and SCID-II=Structured Clinical Interview for DSM IV axis I and II [24,25]; SCL-90-R = Symptom-Check-List 90-R [26]; DAS = Dysfunctional Attitudes Scale [27,28]; DEQ = Depressive Experiences Questionnaire [29,30]; SOFAS = Social and Occupational Functioning Assessment Scale [31]; IIP-32 = Inventory of Interpersonal Problems, 32-item version [32,33]; F-SozU K-14 = Fragebogen zur sozialen Unterstützung, 14-item version [34]; SF-12 = Fragebogen zum Gesundheitszustand (quality of life) [35]; CTQ = Childhood Trauma Questionnaire [36,37]; LIFE-Interview = Longitudinal Interval Follow-up Evaluation [38].

Note: Additionally assessed at all time points of measurement: pharmacological treatment, somatic diagnoses; at T0: previous treatment for depression; at T1: documentation of treatment received (dose, components); T2 and T3: further outpatient treatment, days of sick leave, number of contacts to health care system.

### Objectives and hypotheses

First, the study aims to describe changes in depressive symptomatology during and after psychosomatic inpatient and day hospital treatment for depression and to identify subgroups with a good or less favourable symptom course (observational) including follow-up assessments.

Secondly, inpatient and day clinic treatment will be compared (matched samples). It is assumed that type of depression according to S. Blatt (introjective/high level of perfectionism vs. anaclitic/high level for dependency) is associated with differential outcome in each setting.

### Outcomes

The Quick Inventory of Depressive Symptomatology QIDS-C (expert rating) is chosen as the main outcome criterion. The QIDS is a 16-item version of the Inventory of Depressive Symptomatology (IDS), which shows high correlations with other instruments for the measurement of depressive symptomatology [23]. It´s a common, internationally used, licence-free instrument which has a self-report and an expert rating form [23]. The QIDS was chosen as its total score is also used as the main outcome criterion in a large trial on outpatient psychotherapy for chronic depression that is currently conducted in Germany (“LAC-study”, [39]).

We aim to assess outcome dimensionally (change on the QIDS-C score from admission to the three-months follow-up) as well as categorically: a symptom reduction < 20% is defined as “no effect”, a symptom reduction between 20% and 50% as modest change, a symptom reduction of > 50% as partial remission and a symptom reduction of 100% as complete remission (falling below the cut-off value of depression of the QIDS-C) [3,40].

### Sample size calculation

The power calculation is based on assumptions about differences in the frequencies of remissions by treatment setting, the difference of means on the outcome measure, attrition and loss of cases due to mismatches. Given the probability of remission was p=0.30 for treatment A and p=0.45 for treatment B, then for equal *N* in each group, α = .05 and (1-β) = 0.80, the required sample size is *N* =180 (each group; calculated with PASS2008). For a standardized difference of *d* = 0.2 (small effect size) and α = .05 and (1-β) = 0.80, the required sample size is *N* = 200. With an attrition rate of 10% and loss due to mismatches of 20% (matching samples for research question II), the total sample size should be increased to *N* = 300 per group. Including covariates, subgroups and nesting (HLM) will help to increase the precision of models.

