### Methods against bias

To compare inpatient and day clinic samples, a parallelization according to known predictors of outcome [14] will be conducted: (1) Gender [m;f], (2) age [<40; >=40: mean age in previous studies], (3) number of additional axis-I diagnoses [<2; >=2], (4) number of previous episodes of major depression [0; <=2; >2] and (5) duration of the recent episode of MDE [<6 months; 6–24 mo >24 mo]. Criteria (1) to (3) will be matched 1:1; criteria (4) & (5) are used as lenient criteria, to be matched 1:1 if possible, otherwise the extremes may not be matched together. We expect a loss of about 20% due to “mismatches”, missing data and patients dropping out of the study.

Antidepressant medication, the initial score of the QIDS-C and the number of psychotherapy sessions following discharge will be controlled for in the final analysis. At the end of the study, patients screened and not taking part and patients taking part in the study will be compared, as well as patients dropping out of the study with those completing the study.

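### N = 200 for d = 0.2 at 80% power fits only about 199 matched pairs with an unstated within-pair correlation near 0.5; a two-group comparison needs about 394 per setting

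*Protocol article*

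**What the plan says.** The Sample size calculation section of the protocol article has two parts. The first concerns remission, 0.30 against 0.45, "for equal *N* in each group", and arrives at 180 per group. The second concerns the mean difference, for a standardized d of "0.2 (small effect size) and α = .05 and (1-β) = 0.80, the required sample size is *N* = 200". This second figure has no test, sidedness, unit (patients per group or pairs), SD or correlation attached.

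The section then allows for losses: "With an attrition rate of 10% and loss due to mismatches of 20" per cent, the latter tied to the matching for the second research question, and so reaches 300 per group. It closes by saying that covariates and nesting will add precision.

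Methods against bias describes the matching. Gender, age split at 40 and number of additional axis-I diagnoses are matched 1:1; number of previous episodes and episode duration are matched leniently. Here a loss of about 20% is expected to cover mismatches, "missing data and patients dropping out of the study". Medication, initial QIDS-C and later psychotherapy sessions are to be controlled for.

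Statistical analysis plans a hierarchical linear model with nested random effects for QIDS-C and controls the change from admission to three months for baseline. No term for the matched pair is named.

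**The concern.** A small effect (d = 0.2) compared between two independent groups at two-sided 5% and 80% power needs nearly 400 per group. The protocol gives about half of that. The surrounding text suggests an ordinary between-group d: the section speaks of a difference of means, calls 0.2 small, gives the remission figure per group and inflates to a number per group.

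The stated sensitivity of the inpatient against day hospital comparison on the main outcome is at stake. If d means the between-setting difference in patient SD units, the 80% is not supported by anything the protocol states. Separately, two sections give different loss allowances for the same matched comparison, so the number available for it is not fixed.

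**Working it through.** **Inputs.** From Sample size calculation: d = 0.2, alpha 0.05, power 0.80, N = 200, losses of 10% and 20%, 300 per group. From Methods against bias: about 20% loss in all. Two-sided testing is assumed, because sidedness is not stated. The within-pair correlation (rho) and the correlation of covariates with the outcome (r) are not in the document and are shown as ranges. Powers and required numbers below are from t-tests unless marked as normal approximation.

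**1. Reproducing 200.** (z0.975 + z0.80)² = (1.960 + 0.842)² = 7.849.
- Paired: 7.849 / 0.2² = 196.2 by normal approximation; the paired t-test gives 198.2, so 199 pairs. This matches 200.
- Two independent groups: 2 × 7.849 / 0.2² = 392.4; the t-test gives 393.4, so 394 per group. One-sided it is 310. Neither matches 200.

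**2. What the paired reading requires.** The SD of a pair difference is SD × √(2(1 − rho)). A paired d of 0.2 is therefore a between-setting d of 0.2 × √(2(1 − rho)), which is 0.28 at rho = 0, 0.25 at rho = 0.2, and 0.20 only at rho = 0.5.

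**3. What the covariate reading requires.** The number per group is 392.4 × (1 − r²). For 200 this needs r² of about 0.49, so r of about 0.7.

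**4. Numbers left from 300.** 300 × 0.9 × 0.8 = 216 (210 if the two losses are added). With 20% overall, 300 × 0.8 = 240. The step from 200 to 300 is itself adequate: 200 / 0.72 = 278. Starting from 394 it would be 394 / 0.72 = 548 per group.

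**5. Unadjusted two-group comparison, between-setting d = 0.2.**

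| Analysed per setting | Power | d detectable at 80% |
|---|---|---|
| 200 | 51% | 0.28 |
| 216 | 55% | 0.27 |
| 240 | 59% | 0.26 |
| 300 (no loss) | 69% | 0.23 |

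**6. With one precision gain (assumed values), d = 0.2.**

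| Assumption | Needed (per group or pairs) | Power at 216 |
|---|---|---|
| covariate r = 0.3 | 359 | 58% |
| covariate r = 0.5 | 296 | 67% |
| covariate r = 0.7 | 202 | 83% |
| within-pair rho = 0.1 | 356 | 59% |
| within-pair rho = 0.2 | 316 | 64% |
| within-pair rho = 0.3 | 277 | 70% |
| within-pair rho = 0.5 | 199 | 83% |

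**7. With both gains.** At assumed r = 0.5 and a residual within-pair correlation of 0.2, the need is about 393 × 0.75 × 0.80 = 236 per group (normal approximation). Power is then about 76% at 216 and 80 to 81% at 240, provided that the analysis uses the pairing.

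**The case against.** The strongest reply is that 200 is not a slip. The comparison is planned on 1:1 matched samples, and a paired test returns 199, so a matched-pairs calculation is a plausible source. Baseline QIDS-C and other covariates will also be controlled, so an unadjusted two-group power is not the power of the planned analysis. A journal article may leave the test, SD and correlation to the full protocol.

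Much of this stands. A reader might infer that the trial simply has 51 to 55% power. The documents do not support that, because the figure applies only to an unadjusted comparison of independent groups. Nor do they show that matching cannot reach a correlation of 0.5. That is doubtful for three coarse criteria and two lenient ones, but no figure in the protocol settles it.

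The reply does not rescue the sentence as printed. It mentions no pairs for this figure, the analysis section names no pair term, and covariates are offered as extra precision on top of the calculation. A required number given for d = 0.2 without the condition that makes it true is misleading even in a condensed article.

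Two further inferences should be left aside. One is that the remission scenario contradicts d = 0.2: the protocol presents them as separate scenarios for two outcomes and never equates them. The remission figure itself is sound (163 per group uncorrected, 176 with continuity correction, against the stated 180). The other is that the trial sets out to show the settings equivalent: it states no equivalence hypothesis.

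The difference in losses is also modest, since 210, 216 and 240 all exceed the stated 200.

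**Conclusion.** The point holds in a conditional form. As a two-group calculation, 200 is about half of the 394 required. As a paired calculation it is right, but then d = 0.2 is a between-setting difference of 0.2 only with a within-pair correlation near 0.5, which the protocol neither states nor supports.

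Power for a between-setting d of 0.2 at 216 per setting is about 55% unadjusted, 58 to 67% for assumed r of 0.3 to 0.5, and 59 to 70% for assumed within-pair correlation of 0.1 to 0.3. It comes close to 80% if both gains are sizeable and the model carries the pairing. These results assume two-sided 5% testing, equal groups and 200 meaning per group, as the inflation to 300 per group implies.

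The loss allowances in the two sections cannot both apply. They leave 216 or 240, a difference of about 4 percentage points in unadjusted power.

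The remission calculation and the recruitment target are not called into question.

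**What to change.** Keep 300 per setting and correct the sample size paragraph in one of two ways.

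- **If a two-group comparison was meant:** state that about 216 analysable patients per setting give 80% power for a between-setting d of about 0.27 unadjusted, and about 55% for d = 0.2.
- **If a paired or covariate-adjusted calculation was meant:** state the test and its sidedness, the SD that defines d and the correlation assumed with its source. Give the matching structure (pair term or covariates) in the hierarchical model, so that the analysis delivers the assumed precision.

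In either case, use one loss assumption in Sample size calculation and in Methods against bias, and say whether drop-out and missing data are inside or outside the 20%. If 240 is the intended number, the unadjusted figures become d of about 0.26 at 80% power and 59% power for d = 0.2.

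The cost is wording and, in the first case, a less favourable power statement. No patients, visits or assessments are added.
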